## Abstract

Photobiomodulation therapy (PBMT) with low-power laser is used for pain relief in several clinical conditions, including temporomandibular disorders (TMD). As musculoskeletal pain often produces changes in motor behavior, it is common for patients with TMD to present limited mandibular movements. To the date, there is no consensus about the optimal dosimetric parameters of PMBT for TMD. This randomized, controlled, double-blind clinical trial aims to evaluate pain relief and mandibular mobility in patients with TMD following treatments with 2 laser wavelengths, red (660 nm) and infrared (808 nm) individually and in combination as compared to a placebo treatment. One-hundred participants presenting myalgia and arthralgia, with disk displacement or not, will be selected based on the Research Diagnostic Criteria for Temporomandibular Disorders. All participants will be instructed about the etiology, prognosis, and self-care techniques for pain control on TMD, and followed up for 2 weeks. After this period, those who still present pain score over 4 in a visual analog scale (VAS) will be included in the study. Participants will be randomly assigned to 4 treatment groups: G1 = placebo (SHAM); G2 = PBMT with red laser (660 nm, 0.034 cm^2^, 88 J/cm^2^, 100 mW, 3 J/point); G3 = PBMT with infrared laser (808 nm, 0.034 cm^2^, 88 J/cm^2^, 100 mW, 3 J/point); and G4 = PBMT with red and infrared laser alternated between sessions. The treatment consists of 8 sessions, 2 times a week. The effect of the proposed therapies will be measured by: pain reduction in VAS; pressure pain threshold on TMJ, masseter and temporal muscles; and the amplitude of mandibular movements (opening, protrusion, and right and left lateral movements). The data will be collected at the following times: initial (T1), after the 1st treatment session (T2), at the end of treatment (T3), and 30 days after the last PBMT session (T4). For statistical analysis will be used 2-way repeated measures analysis of variance test, complemented by a post hoc Tukey test (*P* < .05).

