### Sample size calculation

2.10

Sample size calculation was based on the primary outcome (mean pain reduction from baseline to 4 weeks examination), and based on ANOVA statistical test (4 groups). Considering an 80% power, alpha of 5%, and expecting a standard deviation of 2.5 cm, 23 individuals per group (totaling 92 participants) will be required to detect a minimum difference of 2.5 cm in VAS between the groups. In anticipation of a loss of 10% at follow-up, 100 study participants will be included (25 per group). This calculation was based on a study carried out in Brazil,^[16]^ in which the PBMT was effective in reducing the pain of individuals with TMD. The calculation aimed to detect the difference between the active laser groups and SHAM.

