### Statistical analysis

2.15

Statistical analysis will be conducted to compare the 4 groups of treatment, concerning the change from baseline of primary and secondary outcomes. Regarding the primary outcome, the groups will be compared using test of comparison of means. If there is adherence to a normal distribution and homogeneity of variances, the groups will be compared by analysis of variance (ANOVA; 2-way repeated measures ANOVA with post hoc Tukey Test). The analysis will be performed by intention to treat, with the imputation of data by carrying forward the last observed outcome in the case of missing data.^[26]^ Groups will be compared as regards other outcome using repeated measures ANOVA or a Chi-squared test. All tests will be conducted considering a 5% alpha.

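### The primary ANOVA is used only if the outcome data show normality and equal variances, so the primary method is not fixed in advance

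*Protocol article*

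**What the plan says.** Section 2.15 (Statistical analysis) opens the primary analysis in general terms: "Regarding the primary outcome, the groups will be compared using test of comparison of means". It then adds the condition: "If there is adherence to a normal distribution and homogeneity of variances, the groups will be compared by analysis of variance", with 2-way repeated measures ANOVA and post hoc Tukey tests given in brackets. It names no test or plot for judging the condition. It does not say whether the check is per arm or on residuals, or on change scores or visit scores. The only threshold is general: "All tests will be conducted considering a 5% alpha".

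The Abstract gives the same method with no condition: "For statistical analysis will be used 2-way repeated measures analysis of variance test, complemented by a post hoc Tukey test".

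Section 2.9 (Outcomes and data collection) defines the primary outcome as the fall in VAS from baseline to 4 weeks, reported in centimetres as group means. Section 2.10 (Sample size calculation) is "based on ANOVA statistical test (4 groups") and asks for a difference in the same unit: "23 individuals per group (totaling 92 participants) will be required to detect a minimum difference of 2.5 cm in VAS between the groups".

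**The concern.** The article gives a fixed and a conditional version of its primary analysis. Under the conditional version, the outcome data decide whether the planned test is used. Naming a fallback in another document would not remove this, because the condition itself makes the choice data-dependent.

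The condition may also respond to treatment. VAS cannot go below 0 and entry requires a score above 4, so a large fall in pain piles scores up at the floor. That distorts the shape and spread of the changes in the arms that respond. The checks are then more likely to fail when the lasers work than when they do not.

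At stake is the meaning of the primary result. The outcome and the sample size concern a difference in means. If a rank test replaced ANOVA, the trial would no longer test that quantity.

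**Working it through.** **1. The plan's own figure.** Section 2.10 gives a difference of 2.5 cm, SD 2.5 cm, 80% power, alpha 5% and 4 groups. The pattern of means is not stated. I put two means 2.5 cm apart and the other two midway:

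- f = √[(1.25² + 0 + 0 + 1.25²)/4] / 2.5 = 0.884/2.5 = 0.354
- Noncentrality at n = 23 per group: 4 × 23 × 0.354² = 11.5, with 3 and 88 degrees of freedom; power 80.4%
- At n = 25 per group: noncentrality 12.5; power 84.0%

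The stated 23 per group is the smallest n reaching 80%, so it reproduces. The design is therefore sized on an ANOVA of means.

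**2. How often the condition would fail with ideal data.** Assumption: formal, independent tests at 5%. The chance that at least one of m tests rejects when every assumption holds is 1 − 0.95^m.

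| Checks | m | Formula | Simulated (20,000 trials, n = 23 and 25 per arm) |
|---|---|---|---|
| One normality test on pooled residuals + one variance test | 2 | 9.75% | 8.3% to 10.5% |
| Normality test in each of four arms + one variance test | 5 | 22.6% | 21.5% to 23.9% |
| Plots only | – | not calculable | – |

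The simulations used Shapiro-Wilk and Levene tests. The spread within a row comes mainly from centring Levene's test on the mean or the median.

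**3. With the VAS floor.** From the article: entry above 4, SD 2.5 cm, a 2.5 cm difference, 25 per arm, scale 0 to 10. Assumed, because the article gives no figures: mean change 1.5 cm in sham and 4.0 cm in each laser arm, scores cut at the ends of the scale, and three baseline shapes. The checks are applied to change scores.

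| Assumed baseline | Five tests (per arm) | Two tests (residuals) |
|---|---|---|
| Uniform, 4 to 10 | 29% | 13% |
| Normal centred on 6.5, cut at 4 and 10 | 37% | 23% |
| Normal centred on 5, cut at 4 and 10 | 67% | 58% |

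Repeat runs moved these by only one or two percentage points. For the middle row, with no treatment effect (all arms changing by 1.5 cm), the rates were about 18% and 9%, so the planned effect roughly doubles the chance of failure. With the uniform baseline the rate is only slightly above that for ideal data. The direction of the effect is supported, but its size depends on the assumed baseline.

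**4. What failure does to inference.** I took the procedure one would worry about: ANOVA if all five checks pass, Kruskal-Wallis otherwise.

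| | Conditional procedure | ANOVA always |
|---|---|---|
| Type I error, normal data and floor scenarios | 5.1% to 5.6% | 4.9% to 5.5% |
| Omnibus power, three lasers each 2.5 cm better than sham | 93.8% to 95.2% | 94.8% to 95.6% |

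A further run put type I error at 4% to 6% and power near 95% for both. Power is above the planned 80% because three arms differing from one by 2.5 cm gives f = √3/4 = 0.433, for which the formula gives 95.9% at n = 25.

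**The case against.** The strongest objection is that the condition does little measurable harm. Step 4 bears this out: a reader might infer that letting the data pick the test inflates the false-positive rate or costs power, but in these scenarios neither moves by more than about a percentage point. This part of the objection stands.

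Second, a reader might infer that about one trial in five would lose its planned analysis. The documents do not support that. The figure needs five formal 5% tests, and section 2.15 names none. Residual-based testing halves it, and plots give no rate. Likewise, no single rate under the floor can be claimed, because the article does not give the baseline distribution.

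Third, a missing fallback is no fault in a condensed article, since the full protocol or analysis plan may name one. Nor is a rank-test fallback stated anywhere. The opening sentence of the section, "Regarding the primary outcome, the groups will be compared using test of comparison of means", fits equally well with a Welch-type alternative that keeps the mean difference. This also stands, so the change of estimand is a possibility only.

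What the objection does not remove is the condition itself. It is written into the primary analysis, and the Abstract contradicts it by stating the ANOVA outright.

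**Conclusion.** The point holds as one of pre-specification. Section 2.15 lets the outcome data decide whether the planned primary test is used, while the Abstract, outcome definition and sample size treat a comparison of means as settled.

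Under formal 5% checks, ANOVA would be dropped in about 9–10% (residuals) to 21–24% (per arm) of trials with ideal data. Under a VAS floor the illustrative range is 13–67%. These rates rest on assumed tests and, for the floor, on assumed baselines and changes. Error rates and omnibus power are essentially unaffected. The damage is to the fixedness of the method and, if a rank test were used, to the quantity estimated. The condition also buys little: with equal arms of about 25, comparisons of means tolerate moderate non-normality, and unequal variances can be handled directly. The change is worth making because it is nearly free.

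**What to change.** Delete the conditional clause in section 2.15 and state one primary analysis that applies whatever the checks show: a comparison of 4-week (T3) VAS means between the four groups, adjusted for baseline VAS, with variance-robust (HC3 or Welch-type) standard errors. Keep residual plots and similar diagnostics as description, and list a rank-based or permutation test as a sensitivity analysis only. Bring the Abstract's wording into line.

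Removing the clause alone would cure the data-dependence. The robust standard errors are added so that unequal variances no longer call for a separate decision. The cost is a sentence of text and a very small loss of efficiency at about 25 per arm. The Trial status section reports 40 of the planned 100 participants included, so on the article's own account the change could be made well before the data are complete.

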### Outcomes and data collection

2.9

Evaluations will be performed by a single trained examiner ([name]) who is blinded to the allocation of the participants within the different treatment groups. Measurements will be performed at the following times: initial (T1), immediately after the 1st PBMT session (T2), at the end of the treatment (T3), and 30 days after the end of therapies (T4).

The primary outcome of the study will be pain reduction (baseline – 4 weeks) according to a visual analog scale of 10 cm. Pain reduction will be expressed in centimeter, as mean group values.

Secondary outcomes will be:

1.Pressure pain threshold in the TMJ, masseter, and anterior temporal muscles, bilaterally, with a digital algometer, registered in kgf (Pain Test Algometer FPX 25; Wagner Instruments).2.Extension of mandibular range of movement, such as mouth opening (taking into consideration the overjet), protrusion (added the overbite), and right and left mandibular movement (noting possible midline deviation) in centimeter, with the aid of a digital caliper.

At each PBMT session, spontaneously reported adverse events and other unintended effects of trial interventions will be registered and managed according to the participant's need.

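### The primary outcome and sample size rest on one change score at 4 weeks, but the named repeated-measures ANOVA has no stated visits or deciding effect and, read over T1–T4, is not the test that was powered

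*Protocol article*

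**What the plan says.** Three statements bear on the primary analysis.

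- **Outcome** (Protocol article, 2.9 Outcomes and data collection): "The primary outcome of the study will be pain reduction (baseline – 4 weeks) according to a visual analog scale of 10 cm". Treatment is eight sessions over four weeks (2.8), so this is one number per patient, the change from T1 to T3.
- **Sample size** (2.10): "Sample size calculation was based on the primary outcome (mean pain reduction from baseline to 4 weeks examination". The same sentence gives the method used for sizing: "based on ANOVA statistical test (4 groups". The inputs are "Considering an 80% power, alpha of 5%, and expecting a standard deviation of 2.5 cm", and the result is "23 individuals per group (totaling 92 participants) will be required to detect a minimum difference of 2.5 cm in VAS between the groups". No time factor, number of visits or within-patient correlation is given.
- **Test** (2.15 Statistical analysis): the section first refers to change from baseline and to a comparison of means. It then states that, if the distributional conditions are met, "the groups will be compared by analysis of variance (ANOVA; 2-way repeated measures ANOVA with post hoc Tukey Test".

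The abstract lists the four time points T1 to T4 and continues directly: "For statistical analysis will be used 2-way repeated measures analysis of variance test, complemented by a post hoc Tukey test".

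No section says which visits enter the repeated-measures model. None says whether the group main effect, the group-by-time interaction or a comparison at T3 carries the primary conclusion.

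**The concern.** A two-way repeated-measures ANOVA needs a time factor and yields several F tests. With T1 to T4 in the model, the interaction asks whether the group profiles differ anywhere over four visits. The group main effect asks whether groups differ on average over the visits. Neither question is whether the groups differ in the change from T1 to T3.

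Two things are at stake. First, the stated 80% power was calculated for a different test. Secondly, the main effect, the interaction or a post hoc comparison at T3 could each be presented as the primary result once the data are known. T2 comes right after one session and T4 comes 30 days after treatment ends. A pattern at either visit alone could make the omnibus test significant with nothing at 4 weeks.

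**Working it through.** **Inputs from section 2.10:** difference 2.5 cm, SD 2.5 cm (read as the SD of the change, since the calculation is on pain reduction), alpha 5%, four groups, n = 23 per group.

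**Assumptions, because the article gives no figures:** group means 0, 1.25, 1.25, 2.5 cm (two extreme groups 2.5 cm apart, the others midway); compound symmetry; correlation ρ between visits of 0.3 to 0.7 where it matters.

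**1. The plan's own figure.** For a one-way ANOVA on change, λ = n Σ(μᵢ − μ̄)²/SD². The squared deviations sum to 1.25² + 1.25² = 3.125, so λ = 23 × 3.125/6.25 = 11.5. With df 3 and 88 the critical F is 2.708 and the power is **80.4%**. With n = 22 it is 78.3%, so 23 is the smallest n, as stated. With n = 25 it is 84.0%.

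**2. Repeated-measures model with T1 and T3 only.** The interaction F equals the one-way F on change. On one simulated data set both were 0.6774. λ is again 11.5 and the power 80.4%.

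**3. Four visits, group-by-time interaction.** The residual variance is 2.5²/2 = 3.125. Let pₜ be the fraction of the 2.5 cm effect present at visit t. Then λ = 23 × 3.125 × S/3.125 = 23 S, where S = Σ(pₜ − p̄)²; df are 9 and 264, critical F 1.915.

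- Effect at one visit only: S = 1 − 1/4 = 0.75, λ = 17.25, rejection 83.1%. The answer is the same whether that visit is T2, T3 or T4.
- Effects of 0.5/2.5/1.25 cm at T2/T3/T4: S = 1.29 − 1.7²/4 = 0.5675, λ = 13.05, power 69.0%.
- Effects of 0/2.5/2.5 cm: S = 2 − 2²/4 = 1, λ = 23, power 93.6%.

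**4. Four visits, group main effect on raw scores.** λ = 23 × 3.125 × p̄²/V, with V = [3.125/(1 − ρ)] × (1 + 3ρ)/4. V is 2.121, 3.906 and 8.073 for ρ = 0.3, 0.5 and 0.7. For T3 only, p̄ = 0.25, so λ = 4.492/V = 2.118, 1.150 and 0.556, and power is 19.4%, 12.3% and 8.3%.

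**5. Group main effect on the changes at T2, T3 and T4.** The mean of the three changes has variance 3.125 × (1 + 1/3) = 4.167, whatever ρ is. λ = 71.875 q²/4.167 = 17.25 q², where q is the mean of pₜ over T2–T4.

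Rejection rates at 23 per group:

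| Effect at T2/T3/T4 (cm) | Interaction, T1–T4 | Main effect, raw T1–T4 (ρ 0.7 to 0.3) | Main effect, changes T2–T4 |
|---|---|---|---|
| 0/2.5/0 | 83.1% | 8.3–19.4% | 17.9% |
| 0.5/2.5/1.25 | 69.0% | 15.6–50.7% | 46.4% |
| 0/2.5/1.25 | 79.0% | 13.0–40.5% | 36.9% |
| 0/2.5/2.5 | 93.6% | 20.3–66.1% | 61.2% |
| 1.25/2.5/2.5 | 79.0% | 30.2–86.1% | 82.1% |
| 2.5/2.5/2.5 | 83.1% | 42.4–96.1% | 94.1% |
| 2.5/0/0 or 0/0/2.5 (nothing at T3) | 83.1% | 8.3–19.4% | 17.9% |

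**The case against.** The strongest reply is that section 2.15 does not say that all visits enter. It speaks of change from baseline and a comparison of means, and section 2.9 fixes the change as baseline to 4 weeks. Read together, these allow a model on T1 and T3, which tests the primary outcome exactly and with the stated power. That reading is possible. It is not stated, however, and the abstract names the test directly after listing T1 to T4, so the four-visit reading remains the natural one.

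A reader might infer three stronger things that the article does not support.

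- **That the planned analysis is badly underpowered.** The severe losses belong to the group main effect, and nothing makes that effect primary. The reference to change from baseline also speaks against a raw-score main effect that includes T1. The interaction, the more usual test in such a design, has 69–94% power in the profiles above and falls clearly below plan in only one of them.
- **That the type I error exceeds 5%.** An interaction test without correction can exceed 5% if sphericity fails. With an assumed T1–T2 correlation of 0.85 and the others 0.3–0.6, simulation gave about 8%. But that covariance is assumed, and the article does not say that no correction will be used. With a Greenhouse–Geisser correction, simulated error under similar covariances was 4.4–5.4%.
- **That a significant interaction could never be traced to 4 weeks.** The planned Tukey comparisons could locate a difference at T3. What is missing is a statement that this comparison decides the trial.

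**Conclusion.** The point holds as an undefined primary test that, on its natural reading, is not the one that was powered. The 80% figure is correct for a one-way comparison of the T1-to-T3 change. It was not calculated for either omnibus test of a four-visit model.

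For the interaction the defect is mainly one of attribution: an 83% chance of rejection with no effect at 4 weeks, if 2.5 cm is present only at T2 or only at T4. For the main effect it is dilution by other visits, and its size depends on how early the effect appears and how long it lasts. On raw scores this runs from very low power to power above plan. On change scores it runs from 18% (T3 only) to 94% (full effect at all three visits).

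These figures assume an SD of change of 2.5 cm, compound symmetry, the group means given above and, for the raw-score main effect, a correlation of 0.3 to 0.7. That the four-visit tests do not isolate T3 does not depend on those values.

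**What to change.** In section 2.15 and the abstract, declare the between-group comparison of VAS at T3 as the single primary analysis. Any of these would serve:

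- a one-way ANOVA on the T1-to-T3 change, which matches the sample size calculation directly;
- preferably, an ANCOVA of VAS at T3 adjusted for baseline VAS;
- the T3 contrasts from a longitudinal model, named in advance as primary.

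Make the all-visit repeated-measures analysis and the comparisons at T2 and T4 secondary. If that analysis remains a repeated-measures ANOVA, state how departures from sphericity will be handled.

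The cost is a few sentences, dated before unblinding. No patients, visits or measurements are added. The article reports 40 of the planned 100 participants included at the time of writing.

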### Objectives

2.2

Primary objective:

To evaluate the efficacy of different photobiomodulation protocols (red, infrared, and red associated with infrared laser) on pain of patients with TMD.

Secondary objectives:

To assess the immediate and longitudinal impact of proposed treatments on pain and mandibular mobility.To relate pressure pain threshold (PPT) and pain under visual analog scale during a bilateral palpation examination of the TMJ, temporal and masseter muscles, at different times of the treatment.To verify, 30 days after concluding the PBMT, the duration of the therapeutic effects produced by the proposed protocols.

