### Protocols for PBMT

2.8

All participants will undergo PBMT according to the group to which they were allocated. The assigned group will be only revealed to the researcher responsible for the irradiation ([name]) by the time of the first PBMT session, after the 2-week educational measurements and initial evaluations (T1). The PBMT will be performed twice a week, totaling 8 sessions (4 weeks).

The G1 group (SHAM) will undergo a PBMT simulation. Negative control treatment will be held with a SHAM-equipment (DMC, São Carlos, Brazil) of the same design as the active equipment, simulating a PBMT session since it's able to emit an inert guide light (with no power), and reproduce the time marker's sounds identically to the active one.

The G2 group will be irradiated with an InGaAlP red laser (Therapy XT; DMC), 660 nm, 88 J/cm^2^, 100 mW, 30 s/point, spot size 0.034 cm^2^, 3 J/point, in continuous mode and with the tip positioned at 90° in contact with the skin.

The G3 group will be irradiated with an AsGaAl infrared laser (Therapy XT; DMC), 808 nm, 88 J/cm^2^, 100 mW, 30 s/point, spot size 0.034 cm^2^, 3 J/point, in continuous mode and with the tip positioned at 90° in contact with the skin.

The G4 group will be irradiated in the odd sessions with red laser (InGaAlP, 660 nm), following the G2 protocol; and in the even sessions, with infrared (AsGaAl, 808 nm) as described for the G3 protocol.

The equipment was previously calibrated and the output power is periodically checked using a power meter (Laser Check; MMOptics LTDA, São Paulo, Brazil). A summary of the irradiation parameters is shown in Table 2.

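### Carrying the last observation forward enters a score taken just after session 1 as the 4-week primary result, and assigns zero waning at 30 days to anyone missing the last visit

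*Protocol article*

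**What the plan says.** Protocol article, section 2.15 (Statistical analysis): the analysis is by intention to treat, "with the imputation of data by carrying forward the last observed outcome in the case of missing data". No alternative method or sensitivity analysis is named.

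Section 2.9 (Outcomes and data collection) sets the assessments at "initial (T1), immediately after the 1st PBMT session (T2), at the end of the treatment (T3), and 30 days after the end of therapies (T4"). What it names for recording at the treatment visits is safety only: "At each PBMT session, spontaneously reported adverse events and other unintended effects of trial interventions will be registered". The primary outcome is the reduction in VAS pain from baseline to 4 weeks, which is T3.

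Section 2.8 (Protocols for PBMT) gives 8 sessions, two a week for 4 weeks, so 7 of the 8 sessions fall between T2 and T3.

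Section 2.2 (Objectives) includes, as a secondary objective, "To verify, 30 days after concluding the PBMT, the duration of the therapeutic effects produced by the proposed protocols".

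Section 2.10 (Sample size calculation) expects 10% loss and raises 92 participants to 100.

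**The concern.** Carry-forward does least harm when the last observed value lies close to the endpoint. Here it does not, because no outcome assessment falls between the end of session 1 and the end of treatment. What is carried depends on when the participant leaves:

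- **Lost before T2:** baseline is carried, so the 4-week pain reduction is set to zero.
- **Lost between T2 and T3:** the score after one session of eight becomes the 4-week primary result.
- **T3 observed, T4 missing:** T4 is set equal to T3, so that participant contributes zero waning to the 30-day objective.

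The first two cases affect the primary comparison. If the laser effect builds up over the course, early scores entered as 4-week scores dilute it. If pain improves in all arms during treatment, an arm that loses more participants looks worse for that reason alone. The third case affects the duration objective and the repeated measures model, not the 4-week contrast.

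**Working it through.** **The plan's own figure.** Inputs from section 2.10: 4-group ANOVA, 80% power, 5% alpha, SD 2.5 cm, difference 2.5 cm. Take two group means 2.5 cm apart and the other two at the midpoint. The noncentrality is then λ = n × (2.5/2.5)²/2 = 0.5n, with 3 and 4(n − 1) degrees of freedom. Power is 78.3% at n = 22 and 80.4% at n = 23, so the stated 23 per group reproduces. At 25 per group with no loss it is 84.0%.

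**Assumptions, none given in the documents.** Effect (active minus sham) 0.3 cm at T2 and 2.5 cm at T3; improvement from T2 to T3 shared by both arms 1.2 cm; dropout unrelated to outcome; all the loss considered falls between T2 and T3.

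From T2 to T3 the sham arm then improves by 1.2 cm and the active arm by 1.2 + (2.5 − 0.3) = 3.4 cm. With proportions a (active) and s (sham) lost, the expected difference under carry-forward is

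2.5 − 3.4a + 1.2s.

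| Loss, active / sham | Arithmetic | Expected 4-week difference |
|---|---|---|
| 10% / 10% | 2.5 − 0.34 + 0.12 | 2.28 cm |
| 20% / 20% | 2.5 − 0.68 + 0.24 | 2.06 cm |
| 20% / 5% | 2.5 − 0.68 + 0.06 | 1.88 cm |
| 5% / 10% | 2.5 − 0.17 + 0.12 | 2.45 cm |
| 5% / 20% | 2.5 − 0.17 + 0.24 | 2.57 cm |

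With no laser effect at either time, the difference under carry-forward is 1.2 × (s − a). That is 1.2 × (0.20 − 0.05) = 0.18 cm in favour of laser at 20% sham and 5% active loss, −0.18 cm if the losses are reversed, and zero if they are equal.

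**Power in the sizing model, SD held at 2.5 cm.**

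| Equal loss | Carry-forward, 25 per arm | Observed participants only |
|---|---|---|
| 10% | difference 2.28 cm: 76.0% | 22.5 per arm, 2.5 cm: 79.4% |
| 20% | difference 2.06 cm: 66.3% | 20 per arm, 2.5 cm: 73.7% |

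**Sensitivity to the T2 assumption at 10% equal loss.** If none of the T3 effect is present at T2, the difference is 0.9 × 2.5 = 2.25 cm and power 74.8%. If half is present, it is 2.5 × (1 − 0.1 × 0.5) = 2.375 cm and power 79.7%. If the whole effect is present at T2, there is no dilution.

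**T4.** Within an arm, waning is understated by (proportion imputed from T3) × (true waning). With 10% to 20% imputed and 1.0 to 2.0 cm of true waning, the range is 0.10 × 1.0 = 0.10 cm to 0.20 × 2.0 = 0.40 cm. In the between-arm difference at T4 these terms cancel if loss and waning are equal across arms.

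**The case against.** **The planned loss is small.** At 10%, the shift under the stated assumptions is 2.5 − 2.28 = 0.22 cm. The standard error of a two-arm difference at 25 per arm is 2.5 × √(2/25) = 0.707 cm, so the shift is about 0.3 of one standard error. The 20% rows are twice the planned loss, and the protocol gives no evidence of unequal loss. The same 10% must also cover losses after T3, so the T3 and T4 distortions cannot both reach their 10% values. All of this stands, and it keeps the point below must-fix.

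**Dilution is conservative for efficacy.** This is true when loss is equal and the effect grows after T2. It does not protect against unequal loss, and it costs power that the inflation to 100 was meant to preserve.

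Three stronger readings are tempting and are not supported:

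- **That the standard errors are too small.** For the 4-week contrast they are not. Each carried value is a real, noisy measurement, and mixing T2 with T3 scores widens the spread. With T2 and T3 changes both at SD 2.5 cm, simulation at 10% loss gave a mean model standard error of 0.735 against a true sampling SD of 0.739. The fault is bias in the estimate.
- **That the arm losing more participants fixes the direction of bias.** It does not: at 5% active and 10% sham loss a true 2.5 cm is still diluted, to 2.45 cm. Nor is there always bias: with no effect and equal loss it is zero.
- **That the 30-day result is decided in advance.** At the planned loss about 90% of T4 scores would be observed. Zero waning is imposed only on participants with T3 but not T4.

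**Conclusion.** The concern holds as a should-fix. Carry-forward is written into the current text as the only handling of missing outcomes, and the T1 to T4 schedule makes it a poor fit, because the last value before T3 follows one session of eight.

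The size is modest at the planned loss and grows with it. The 4-week figures rest on an assumed T2 effect well below the T3 effect, on an assumed shared improvement of 1.2 cm where loss is unequal, and on dropout unrelated to outcome. The closer the T2 effect is to the T3 effect, the smaller the dilution. At T4 the understated waning is a within-arm quantity and concerns a secondary objective.

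**What to change.** In section 2.15, replace carry-forward as the primary handling of missing outcomes with one of the following:

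- a mixed model for repeated measures that includes all randomised participants and uses every observed T2, T3 and T4 score, with the T3 contrast as the primary comparison; or
- multiple imputation carried out separately by arm.

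Carry-forward may stay as a sensitivity analysis. A further sensitivity analysis for data missing not at random is optional.

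The cost is revised analysis wording, slightly more programming and reliance on a missing-at-random assumption. No new visits, data or participants are needed. Section 3.1 (Trial status) reports 40 participants included with recruitment continuing, so at that stage the change could still be made before the final analysis.
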